## Abstract

**Introduction::**

Erectile dysfunction refers to the continued inability of the penis to reach and maintain sufficient erections to achieve a satisfactory sex life and last at least 6 months. As part of traditional Chinese medicine, acupuncture has been widely used in clinical practice. In order to evaluate, the exact effect of acupuncture on the clinical efficacy of patients with Post-stroke Erectile dysfunction (PSED), this experiment uses randomized controlled experiments.

**Methods/design::**

This pragmatic randomized controlled trial will recruit 103 patients who are diagnosed with PSED. Simple randomization to conventional treatment with a 1:1 allocation ratio will be used. Ten 30-min acupuncture sessions will be provided to patients assigned to the Intervention group. All participants will continue to receive conventional treatment. The selection of outcomes will be evaluated by International Erectile Function Index-5 (IIEF-5) score at week 8.

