### Sample size calculation

2.5

According to the clinical experience, the effective rate of PSED in the intervention group was *P*1 = 0.80. The PSED effective rate of the control group was *P*2 = 0.50 (([two-sided type I error rate of 0.05, α = 0.05]; [one-sided type I error rate of 0.10, β = 0.10]). Substituting *f* (α, β) into the formula is as follows: n1 = n2 = 10.5 × (0.8 × 0.2 + 0.50 × 0.35) ÷ 0.152 = 48. The lost follow-up rate of patients will be controlled at 10%, so an additional 5 cases are added to each group. n1 = n2 = 53, that is, 53 cases will be taken from each of the intervention group and the control group. According to Cohen, this effect size is considered “moderate.”

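### The abstract's recruitment total of 103 conflicts with the 106 (53 per group) derived in section 2.5; the cost in power is about 0.8 percentage points

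*Protocol article*

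**What the plan says.** The abstract (Methods/design) states: "This pragmatic randomized controlled trial will recruit 103 patients who are diagnosed with PSED". The next sentence adds: "Simple randomization to conventional treatment with a 1:1 allocation ratio will be used".

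Section 2.5 (Sample size calculation) builds its own total. It takes an intervention rate, "the effective rate of PSED in the intervention group was *P*1 = 0.80", and a control rate, "The PSED effective rate of the control group was *P*2 = 0.50", with "two-sided type I error rate of 0.05, α = 0.05" and β = 0.10. From these it reports 48 per group. It then allows for loss: "The lost follow-up rate of patients will be controlled at 10%, so an additional 5 cases are added to each group". The conclusion is that "53 cases will be taken from each of the intervention group and the control group".

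**The concern.** The article gives two totals for the same trial: 103 in the abstract, and twice 53, or 106, in section 2.5. Both stand in complete sentences of the current text, so neither article condensation nor damage from reading the PDF explains the difference.

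The recruitment total says when enrolment ends, and a later report will be checked against it. With two totals on record, stopping at either could be presented as planned. There is also a question of whether the smaller total, after the planned loss, still delivers the evaluable number on which the 90% power rests.

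**Working it through.** **Inputs.** All are from section 2.5 except the total of 103, which is from the abstract.
- p1 = 0.80, p2 = 0.50
- two-sided α = 0.05
- β = 0.10, taken as 90% power. The text labels it "one-sided type I error rate of 0.10, β = 0.10", but the symbol β and the multiplier 10.5 identify it as the type II error rate.
- 48 evaluable per group; 10% loss; 53 recruited per group
- abstract total 103

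**Step 1: reproduce the 48.** The unpooled two-proportion formula is n = f × [p1(1 − p1) + p2(1 − p2)] / (p1 − p2)², with f = (1.960 + 1.282)² ≈ 10.5.

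n = 10.5 × (0.16 + 0.25) / 0.09 = 47.8, rounded up to 48. The stated 48 follows from the stated rates.

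The expression as printed does not give it. It uses 0.50 × 0.35 where the stated rates require 0.50 × 0.50, and 0.152 as divisor where they require 0.30² = 0.09:
- divisor 0.152: 10.5 × 0.335 / 0.152 = 23.1
- divisor read as 0.15² (a superscript may have been lost in the text): 10.5 × 0.335 / 0.0225 = 156.3

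**Step 2: the totals.** 2 × 53 = 106, which differs from 103 by 3.

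**Step 3: evaluable patients after 10% loss.**
- 103 × 0.9 = 92.7, or 46.35 per group
- 106 × 0.9 = 95.4, or 47.7 per group
- To keep 48 per group (96 in all), loss may be at most 1 − 96/103 = 6.8% from 103, or 1 − 96/106 = 9.4% from 106.

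The 106 falls just short because the plan adds about 10% of 48 (48 × 1.10 = 52.8, rounded to 53). Dividing by 0.90 gives 53.3, rounded up to 54 per group.

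**Step 4: power for 0.80 versus 0.50.** With the same unpooled formula, power = Φ(0.30 / √(0.41/n) − 1.960).

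| Case | Evaluable per group | 0.30/√(0.41/n) | Power |
|---|---|---|---|
| Planned | 48 | 3.246 | 90.1% |
| 106 recruited, 10% loss | 47.7 | 3.236 | 89.9% |
| 103 recruited, 10% loss | 46.35 | 3.190 | 89.1% |

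Difference between 106 and 103: 89.9 − 89.1 = 0.8 percentage points.

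**Step 5: check against the named test.** Section 2.7 names the chi-square test for count data. Exact binomial enumeration of the uncorrected chi-square test, using whole patients, gives:
- 48 + 48: 88.5%
- 47 + 48 (about 95 evaluable, from 106): 88.2% to 88.8%, depending on which group is larger
- 46 + 47 (about 93 evaluable, from 103): 87.3% to 88.0%

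The step from 106 to 103 is again just under 1 point. The figure is already below 90% at the full 48 per group, so most of the gap to 90% comes from the approximation used to size the trial and not from the choice between 103 and 106.

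**The case against.** The strongest reply is that section 2.5 is the operative derivation and fixes 53 per group without ambiguity, so 103 in the abstract is a slip with no practical effect. Recruitment had not started (sections 2.9 and 4), so nothing had yet been decided on it. The loss in power is under one point. Adding 10% instead of dividing by 0.90 is a common convention that changes the result by one patient per group. Most of this stands, and it is why the point is minor. It does not remove the conflict, since both totals are current text.

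Three stronger readings are tempting, and the document does not support them:
- A reader might infer that 103 is impossible because an odd number cannot be split equally. The abstract specifies simple randomization, under which 1:1 is an allocation probability and group sizes vary by chance. An odd total is compatible with that, and 106 would not guarantee 53 and 53.
- A reader might infer from chi-square power below 90% that the abstract's total leaves the trial underpowered. That shortfall is present at 48 per group too, and the unpooled formula is a standard method.
- A reader might infer that correcting 103 to 106 secures 48 evaluable per group. It does not quite do so: 10% loss leaves 47.7.

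One further caution stands. The 0.35 in the printed formula, together with a divisor of 0.15², would fit a control rate of 0.65. That is an inference, not something the article states, but it means the power figures hold only if 0.80 versus 0.50 is confirmed.

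**Conclusion.** The conflict is real: 103 in the abstract against 106 from section 2.5, with nothing to reconcile them. Under the planned 10% loss both totals leave slightly fewer than 48 evaluable per group (about 46.4 and 47.7). Power by the unpooled formula is 89.1% and 89.9%, against 90.1% at 48. The discrepancy between the totals is worth about 0.8 percentage points, so this is a minor correction of a stated sample size.

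The mismatch of totals depends on no assumption. The power figures assume rates of 0.80 and 0.50, two-sided α of 0.05, loss of exactly 10% spread evenly over the groups, and near-equal group sizes.

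**What to change.** 1. Reconcile the expression printed in section 2.5 with the stated rates (the term 0.50 × 0.35 and the divisor), and confirm which control rate was intended. Do this before restating any total or power.
2. If 0.80 versus 0.50 and 48 per group are confirmed, state one total in the abstract and in section 2.5: 106, that is 53 per group.
3. Say that about 47 to 48 per group are expected to be evaluable after 10% loss.
4. Restate power at that evaluable number and name the method: about 89.9% by the unpooled formula, or about 88% by exact calculation for the uncorrected chi-square test. If the sponsor wants 48 evaluable per group after a full 10% loss, the arithmetic gives 54 per group, 108 in total.

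The cost is a text correction made before recruitment starts and, at most, a slightly lower power figure. If step 1 shows that a different control rate was meant, the sample size itself has to be recalculated, which is a larger matter than this point.

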**Discussion::**

This trial may provide evidence regarding the clinical effectiveness, safety, and cost-effectiveness of acupuncture for patients with PSED.

**Trial registration::**

ClinicalTrials.gov, ChiCTR2000030231, Registered on February 25, 2020.

## Introduction

1

Erectile dysfunction (ED) refers to the continued inability of the penis to reach and maintain sufficient erections to achieve a satisfactory sex life and last at least 6 months.^[1]^ It is one of the most common types of male sexual dysfunction. It is also a common and frequently occurring disease in andrology, and it is increasing year by year.^[2]^ Based on the epidemiological studies of ED at home and abroad, it can be found that from the early 1990s to 2010, the prevalence of ED in men over 40 years of age has increased significantly.^[3]^ Although most surveys show that the prevalence of ED has a significant positive correlation with age, the majority of ED patients who come to andrology clinics are 30 to 60 years old. At the same time, it can be seen that long-term smoking and drinking, as well as cardiovascular diseases (CVD), endocrine diseases (diabetes and hyperlipidemia), etc have become high-risk factors affecting the incidence of ED, and the proportion has gradually increased. In contrast, men under 60 still have a strong need for sex and are willing to actively seek the help of a doctor.^[4]^ In contrast, the proportion of organic ED has increased significantly, has become the main type of ED, and has gradually moved forward with the age of high-risk factors. The age of the first occurrence of ED also continues to advance, and the course of disease continues to prolong.^5^,^6^ This has caused the problem that male erectile function and sexual needs of this age group are difficult to match, which seriously affects the quality of life of patients.

Previous studies have shown that ED and many CVD have common risk factors. Risk factors for CVD, such as age, body mass index, cholesterol, triglyceride smoking, hypertension, and smoking, were significantly correlated with ED. In addition, diabetes increases the risk of both, and endothelial dysfunction and arteriosclerosis are common features of both.^[7]^ Autonomic hyperfunction and altered hormone levels may be more complex mechanisms. The close correlation between CVD and cerebrovascular disease in terms of pathogenesis, pathophysiology, and prognosis has been recognized by the medical community.^[8]^ Therefore, it is reasonable to believe that ED is similarly related to cerebrovascular disease. With the change of people's life rhythm and eating habits, many major diseases that affect people's physical and mental health, such as CVD, digestive system diseases and malignant tumors, have a tendency to be younger, which is a hot and difficult point in clinical research. Stroke, also known as cerebrovascular accident, is a cerebrovascular disease with common neurological deficits and brain tissue damage caused by various inducing factors.^[9]^ The disease is characterized by high disability, high mortality and recurrence. Stroke, as an acute cerebrovascular disease, is the leading cause of death and disability in urban and rural residents. Previous studies on stroke have mainly focused on stroke mechanisms, high-risk factors, and treatment, and there have been fewer studies on sexual life dysfunction in patients with stroke. And young and middle-aged male stroke patients often have very high requirements for quality of life; patients are ashamed to open their teeth when they have secondary dysfunction, and the attention of medical staff and related knowledge reserves are relatively small, which seriously affects the treatment of patients. Acupuncture is safe, economical, accurate, convenient to operate, and has small side effects.^[10]^ It has unique advantages in limb dysfunction after stroke. Studies have shown that acupuncture therapy can stimulate the body's internal organs and immune functions, and can adjust physical skills in multiple forms, functions, and levels.

Based on the current needs of patients with Post-stroke Erectile dysfunction (PSED) that do not respond well to conventional treatments, and the need for clinical research on the level of evidence for efficacy, it is worthwhile to further explore the treatment model of acupuncture for PSED. Therefore, we will evaluate the clinical effectiveness and safety of acupuncture in the diagnosis and treatment of PSED. We hope that the results of this study will provide clinicians with acupuncture treatment for PSED and more treatment options.

## Methods/design

2

### Study design and settings

2.1

This study will be a single-blinded, randomized controlled trial with 2 parallel groups. It will be conducted at the Dongzhimen Hospital Affiliated to Beijing University of Chinese Medicine, Beijing, China. This protocol was written and based on Standard Protocol Items: Recommendations for Interventional Trials guidelines. The participants will be informed about the research, procedures, risks, and benefits. If they agree, they will sign an informed consent form. Only those participants who read and agree to the protocol and who sign the informed consent form will take part of the study, following the schedule described in Figure 1.

**Figure 1 F1:**
[figure not shown]
SPIRIT figure for the schedule of enrollment, interventions, and assessments.

**Figure 2 F2:**
[figure not shown]
Study design flow chart.

#### Diagnostic criteria

2.2.1

Western medicine diagnosis refers to “Chinese Urological Disease Diagnosis and Treatment Guide” and “Urinary Surgery” in ED-related diagnostic standards. The diagnosis of TCM refers to the “Guiding Principles for Clinical Research of New Chinese Medicines,” and the syndrome is identified as damp-heat-stasis syndrome type. Western medicine standards refer to the “Guide to the Diagnosis and Treatment of Integrated Chinese and Western Medicine of Chinese Cerebral Infarction” by the Chinese Society of Integrated Traditional Chinese and Western Medicine. Traditional Chinese Medicine refers to the “Stroke Diagnosis and Efficacy Evaluation Standards” formulated by the Chinese Medicine Administration's Encephalopathy Acute Scientific Research Collaboration.

#### Inclusion criteria

2.2.2

This study will be conducted in China. Patients will be recruited from urology/neurology departments of Dongzhimen Hospital Affiliated to Beijing University of Chinese Medicine. We will enroll participants based on the following inclusion criteria:

1.Those who meet the western medical diagnostic criteria for impotence (ED) and occur after stroke;2.20 ≤ age ≤ 60 years old male, normal sexual desire;3.The vital signs are stable and the stroke recovers;4.All are first stroke.5.Accept and sign the informed consent

#### Exclusion criteria

2.2.3

Patients will be excluded if they meet the following criteria:

1.Sexual dysfunction exists before the patient's stroke;2.Stroke patients with vascular malformations (arteriovenous fistula, arteriovenous malformations, aneurysms) and subarachnoid hemorrhage;3.People with neurological diseases and nervous system infections;4.Complicated sexually transmitted diseases;5.People with severe liver and kidney damage;6.Malignant tumor.

#### Conditions for participants to suspend and withdraw from the clinical trial

2.2.4

Researchers participating in clinical trials should carefully record the reasons for the suspension of the trial and the relationship with the clinical trial. It is necessary to clearly record the unwillingness of the subjects to continue the clinical trials, put forward the reasons for withdrawing from the clinical trials, and record the evaluation indicators at the time of discontinuation in detail.

1.Those who cannot adhere to treatment;2.Allergic reactions or serious adverse reactions during the test, the test should be suspended:3.Those who have not been treated strictly according to the plan;4.People who withdrew from the study on their own

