### Interventions

2.3

Control group: The control group will be given conventional treatment to regulate blood pressure, blood glucose, and blood lipid. At the same time, drugs such as nutritional nerves, promoting blood circulation, and removing blood stasis are used, adjusted according to the needs of the disease, and routine rehabilitation training is performed.

Intervention group: This group of patients will be given acupuncture combined with rehabilitation training. TCM acupuncture therapy: Acupoints include *Quchi*, *Waiguan*, *Hegu*, *Dicang*, *Sanyinjiao*, and *Zusanli*. The twisting technique will be used, leaving the needles for 30 min, and treated once a day for 2 weeks. Rehabilitation training is first of all passive activities. With the help of ropes, sticks and other tools, fists, leg lifts, cross fingers, etc are performed 3 times a day for 30 min each time. When the muscle strength returns to level 3, take active training, including voluntary turning, sitting exercises, standing exercises, walking training, etc. The total application time will be 8 weeks. At the same time, closely monitor the change of the condition in order to control the deterioration of the condition in time.

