#### Primary outcome measures

2.4.1

We will use the International Erectile Function Index-5 (IIEF-5) as the main outcome indicator.

1.Recovery: IIEF-5 score ≥22 points after treatment2.Significant effect: IIEF-5 score < 22 points after treatment, points improved ≥60%;3.Effective: IIEF-5 points <22 points after treatment. The improvement of points is between 30% and 60%;4.Ineffective: IIEF-5 points after treatment are <22 points, and the improvement of points is <30%. Total effective rate = (healed + markedly + effective)/total number of cases × 100%.

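### Withdrawing patients for non-adherence or deviation after randomisation, with no stated week-8 follow-up, can bias the primary comparison

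*Protocol article*

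**What the plan says.** Section 2.2.4 of the protocol article is headed "Conditions for participants to suspend and withdraw from the clinical trial". Its list includes condition 1, "Those who cannot adhere to treatment", and condition 3, "Those who have not been treated strictly according to the plan". Condition 4 covers patients who leave by their own choice, so conditions 1 and 3 reach patients who did not ask to leave. Condition 2 concerns suspension for allergic or serious adverse reactions and is not part of this point.

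For patients who stop, the section asks staff to note the reason and to "record the evaluation indicators at the time of discontinuation in detail". It says nothing about a later assessment.

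The abstract (Methods/design) sets the outcome as the "International Erectile Function Index-5 (IIEF-5) score at week 8" and calls the trial pragmatic. Section 2.4.1 defines the primary summary as "Total effective rate = (healed + markedly + effective)/total number of cases × 100", without saying which patients make up the total. Section 2.5 allows for 10% loss by adding 5 patients per group. Section 2.7 names the tests but not the patients to whom they apply.

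**The concern.** Non-adherence and departure from planned treatment happen after randomisation and may depend on both the assigned treatment and the response to it. If such patients leave the trial and are not assessed at week 8, the patients who remain are no longer the two groups that randomisation made comparable. The 5 extra patients per group restore numbers, not comparability.

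The rule could well act differently in the two arms. Only the acupuncture arm has needling to miss, described in section 2.3 as "leaving the needles for 30 min, and treated once a day for 2 weeks". The control drugs may be adapted to the patient's condition, which makes a departure from plan harder to define. Patients and therapists are unblinded (section 2.6).

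What counts as strict compliance is also unclear: the abstract gives ten sessions, while section 2.3 gives daily treatment for two weeks. Those passages must be reconciled, because until they are, unblinded staff have to judge who has breached the plan.

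At stake is the primary result. A week-8 score that was never collected cannot be recovered by any later analysis plan.

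**Working it through.** **1. The passages side by side**

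| Question | What the article states |
|---|---|
| Who is withdrawn? | Non-adherent patients and those not treated strictly to plan, apart from those who leave by choice (2.2.4) |
| What is recorded for them? | Reason, and outcome measures at discontinuation (2.2.4) |
| When is the primary outcome? | Week 8 (abstract) |
| Who is in the denominator? | Not specified (2.4.1) |
| Are withdrawn patients analysed? | Not stated in either direction |

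**2. The plan's own numbers**

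Section 2.5 assumes effective rates of 0.80 and 0.50, two-sided α = 0.05 and β = 0.10, with multiplier 10.5:

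n = 10.5 × (0.80 × 0.20 + 0.50 × 0.50) ÷ (0.80 − 0.50)² = 10.5 × 0.41 ÷ 0.09 = 47.8, so 48; adding 5 gives 53 per arm.

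The stated 48 and 53 therefore follow from the stated rates. The expression as printed uses other numbers, which is a separate matter. This step only supplies the arm size for the illustration. The allowance of 5 per arm serves as a plausible number of withdrawals.

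**3. Illustration under no true effect**

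Assumptions, none of them in the article except the arm size and the 50% control rate: 50% effective in both arms; 53 per arm; 5 patients withdrawn from acupuncture only and left out of the analysis; a proportion r of those 5 would have responded.

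Expected rate among the remaining 48 = (53 × 0.50 − 5r) ÷ 48 = (26.5 − 5r) ÷ 48.

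The rejection probability is found by exact enumeration of two binomials (48 and 53 patients) with the uncorrected chi-square test at 1.96.

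| r | Acupuncture rate | Shift (points) | Two-sided error | Of which favouring acupuncture |
|---|---|---|---|---|
| nobody removed (53 vs 53) | 50.0% | 0 | 4.4% | 2.2% |
| 0 | 26.5/48 = 55.2% | +5.2 | 8.1% | 7.4% |
| 0.25 | 25.25/48 = 52.6% | +2.6 | 5.7% | 4.4% |
| 0.50 | 24/48 = 50.0% | 0 | 4.9% | 2.5% |
| 0.75 | 22.75/48 = 47.4% | −2.6 | 5.7% | 1.3% |

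If exactly 5 non-responders are struck from a full arm of 53, instead of drawing 48 patients at the shifted rate, the first removal row becomes 8.9%, of which 8.1% favours acupuncture. Hence 8–9% for that case.

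If 5 patients with r = 0 are removed from each arm, both rates are 55.2%, the shift is zero and the two-sided error is 5.1%.

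**4. A larger withdrawal**

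Striking 10 non-responders from acupuncture alone gives 26.5/43 = 61.6% and a two-sided error of 22.6%. This is twice the planned allowance and an extreme, not an expectation.

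**The case against.** A reader might infer that the plan prescribes a completers-only analysis. The text does not support that. No section says that withdrawn patients are left out, and none says that they are kept. Recording outcome measures at discontinuation is compatible with using those values, and the unspecified denominator could mean everyone enrolled. Analysis sets and the handling of missing scores may also properly sit in a plan that is not shown. This stands, and the point does not rest on those omissions.

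A reader might also infer that the rule is bound to favour acupuncture. That is not shown either. Controls have drugs and rehabilitation to miss, the needling described in section 2.3 lasts two weeks of an 8-week course, and unblinded controls may leave because they were not offered acupuncture. The article gives no withdrawal rates by arm.

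Finally, the list can be read as a loosely worded set of reasons to be recorded, especially as condition 4 describes an event and not a rule. The heading weighs against this, since it speaks of leaving the trial and not only of stopping treatment. The section does not forbid a week-8 assessment, but it does not provide for one.

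What survives is the conduct rule. It ties trial participation to adherence and states no week-8 assessment for those affected. An analysis plan cannot supply data that were not collected.

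**Conclusion.** The point holds in this form: as written, section 2.2.4 lets post-randomisation behaviour end trial participation before the week-8 primary outcome, and section 2.4.1 does not tie the denominator to all randomised patients. The comparison can therefore be biased. Whether it will be depends on who is withdrawn and on whether they are analysed, neither of which the article settles.

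The size is conditional. With 5 patients withdrawn from acupuncture only and left out, and no true effect, the two-sided error lies between about 5% and 9% as the share of them who would have responded falls from 50% to none. Above 50% the shift runs against acupuncture. It vanishes if withdrawals are equal and alike in both arms. A bias towards acupuncture requires that needling lead to more withdrawals of non-responders in that arm, which is plausible but not documented.

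**What to change.** - Reword conditions 1 and 3 of section 2.2.4 as recorded treatment discontinuations or protocol deviations that do not end trial participation.
- State that week-8 IIEF-5 and the ADL score are collected from every randomised patient who has not withdrawn consent, whether or not treatment was completed.
- In section 2.4.1, define the denominator as all randomised patients, each in the assigned arm. Keep any per-protocol analysis as supportive only.
- Leave condition 2 and all decisions on stopping treatment as they are.

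The cost is a wording change and a week-8 questionnaire for patients who stopped treatment. The estimate may also turn out less favourable than one confined to adherent patients. The article states that recruitment has not started, so the change can be made before any outcome is lost.
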